### Randomisation, allocation concealment and blinding

Following enrolment, participants will be randomised by a designated research scientist who has no role in the trial to either the intervention or control group using a [1:1] ratio allocation within permuted blocks. The randomisation sequence was created using the R Package randomizeR [35] and is concealed from the staff involved in enrolment, consent and all data collection. The randomisation sequence is protected by an electronic password known only to the designated research scientist. The intervention and control solution will be prepared by the designated research scientists who are not involved in the collection of outcome measures or other study procedures. All other members of the participants treating team, including doctors, nursing staff, dietitians and physiotherapists, are blinded to the treatment group.

### Baseline data collection

Following enrolment, baseline data will be collected. This includes demographic data (age and sex), pre-morbid place of residence and employment status, Katz Activities of Daily Living (ADL) index [36] (prior to the ICU admission), illness severity (Acute Physiology, Age, Chronic Health Evaluation II (APACHE II) [37], Australian and New Zealand Risk of Death score (ANZROD) [38] and Injury Severity Scale (ISS) [39], baseline anthropometric data (weight, height, body mass index (BMI)) and nutrition status (assessed using the Subjective Global Assessment (SGA)) [40, 41].

### Standard nutrition practice

At this facility, nutrition provision is commenced in the ICU according to a protocol (Appendix 17). Nutrison Protein Plus® 1.25 kcal, Nutricia, Wuxi, China), providing 63 g protein and 1250 kcal per litre, is the standard nutrition formula and will be commenced at 25 kcal/kg of ideal body weight (IBW) [42]. IBW is defined as body mass index (BMI) between 18.5 and 25 kg/m^2^ for 18–65 years and 22–27 kg/m^2^ for > 65 years. For underweight participants, actual weight will be used. For obese patients with a BMI > 32 kg/m^2^, IBW + 25% (actual weight – IBW) will be used [43]. For patients who are likely to remain intubated for > 7 days and do not meet contraindications [44], a dietitian will measure energy expenditure (MEE) using indirect calorimetry using E-sCOVX (GE, Helsinki, Finland) [45]. Weight-based equations are used to determine estimated protein requirements and are set at 1.2–2.0 g/kg/day [42]. A dietitian will regularly assess nutrition requirements and adjust protein and energy targets on an individual basis as clinically indicated as part of standard nutrition care at this facility.

### Trial intervention and control

The trial intervention is β-hydroxy-β-methylbutyrate (HMB). HMB has been purchased from Myprotein (Warrington, UK). Three grams of HMB is dissolved in 150 ml of fluid. To ensure blinding of participants is maintained, orange juice is the fluid for those allowed oral intake and water for those being enterally fed. Orange juice completely masks the taste and smell of the HMB supplement. HMB powder dissolves completely in water and does not impact the viscosity of the solution. The control is 150 ml of orange juice for those allowed oral intake, or 150 ml of water for those being enterally fed. If a patient is restricted to ingesting only thickened fluids and unable to receive the intervention/control via an enteral feeding tube, Flavour Creations™ orange juice thickened to the appropriate viscosity will be used to blind the intervention/control.

Patients will receive the intervention or control from day 1 post enrolment until hospital discharge or study day 28, whichever occurs first. If a patient is readmitted to hospital within 28 days from randomisation, study procedures and administration of the intervention or control will resume. The intervention or control will be documented in the electronic medication record by the treating team and administered by the nurse caring for the patient. The number of doses prescribed and consumed will be recorded for the duration of the study. The nurse caring for the patient will document patient compliance with the intervention or control and any tolerance issues voiced by the patient believed to be associated with the consumption of trial supplement. The reason for any missed doses will be recorded.

The investigator/s, patient, nurse and member of the treating team will be surveyed on day 1 post enrolment and then day 28 or hospital discharge, whichever occurs first, as to their blinding to the intervention/control as part of the feasibility criteria. All will be invited to take their best guess of whether the participant is receiving the intervention or placebo.

### Outcome measures

Primary and secondary outcome measures will be captured by trained study investigator/s. Summary study schedule and outcome measures are detailed in Table 2. Any outcome data for weight, nutrition status, appetite, muscle mass, muscle strength or physical function, collected within ± 48 h of the specified time points from day 0 to day 28 will be used for this feasibility study. For practical reasons, it may not always be possible for patients to return to hospital on the exact 90-day follow-up time point. Therefore, any data collected within a 2-week window of the “90 day” follow-up measure will be used, and date of measure recorded.

**Table 2 Tab2:** Study schedule and outcome measure

	Assessment/Procedure	Screening and enrolment (day 0)	Day 1, then weekly until day 28 or hospital D/C	Daily from day 1–day 28 or hospital D/C	Day 1	Day 0 until ICU D/C and then 7 days post ICU D/C	ICU D/C	Day 28 or hospital D/C	Day 90 post enrolment
**Study procedures**	Informed consent	**X**							
	Demographic data, APACHE II, ANZROD and ISS, baseline creatinine and urea	**X**							
	Anthropometric data (weight, height and BMI)	**X**							
	Body weight		**X**						**X**
	Nutrition status (SGA)	**X**						**X**	**X**
	Muscle mass		**X**						**X**
	Handgrip strength		**X**						**X**
	Physical function (IMS and mILOA)						**X**	**X**	
	Physical function (PFIT-s)						**X**		
	Patient-reported appetite		**X**						**X**
	Nutrition intake					**X**			
	Administration of intervention/control			**X**					
	Blinding survey				**X**			**X**	
	ICU LOS, days of mechanical ventilation, hospital LOS, discharge destination, use of renal replacement therapy, highest creatinine and urea							**X**	
	Quality of life survey								**X**
	Place of residence and employment status	**X**							**X**
	Mortality							**X**	**X**

*ANZROD* Australian and New Zealand Risk of Death score, *APACHE II* Acute Physiology, Age, Chronic Health Evaluation II, *BMI* body mass index, *IMS* ICU Mobility Scale, *ISS* Injury Severity Scale, *LOS* length of stay, *mILOA* modified Iowa Level of Activity, *PFIT*-*s* Physical Function ICU Test-Scored, *SGA* Subjective Global Assessment

#### Primary outcomes

The feasibility of administering the intervention or control will be quantified as:Successful blinding of the intervention determined through patient and clinician surveysRecruitment and retention rates analysed for patients who meet all inclusion and none of the exclusion criteriaThe amount of HMB supplementation actually consumed compared to the amount intended with full protocol compliance

The following feasibility indicators will be reported:Percentage of surveyed clinicians are able to correctly identify the interventionPercentage of patients who meet all of the inclusion and none of the exclusion criteria are recruited and % of enrolled patients retained until hospital discharge; andPercentage of the prescribed HMB supplementation doses consumed

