### Study participants

Fifty participants who are admitted to the ICU due to traumatic injury will be recruited over an 18-month period (September 2020–February 2022). If participant recruitment is significantly less than this, the study can be extended for an additional 6–12 months. Patients will be screened following admission to ICU and identified as eligible according to the criteria presented in Table 1.

**Table 1 Tab1:** Inclusion and exclusion criteria

**Inclusion:** Adults, ≥ 18 years of age Completed two full calendar days in ICU The predominant reason for ICU admission was a traumatic injury Allowed enteral/ oral nutrition at the time of randomisation	
**Exclusion:** Death during ICU admission deemed to be inevitable Bilateral above knee amputation Patients assessed as requiring completely or predominantly parenteral nutrition Pregnancy Primary neuromuscular pathology present or strongly suspected this admission episode Presumed transection of the spinal cord at any level Medical decision treatment maker, participant or medical practitioner declined consent Limited research availability over enrolment timeframe Enrolment conflict with other research studies Unlikely to be able to participate in long term follow up measures Unable to obtain consent within 7 days from initial traumatic injury	

For study recruitment, consent will be sought from patients wherever they can give consent and it is practicable to approach them. Where it is not practicable to approach a person highly dependent on medical care, or the person is not capable of making such a decision, informed consent will be obtained from the person responsible as per local laws [34]. Consent to continue in the trial will be obtained from the participant if they recover adequately and they are deemed competent. The protocol and consent process has been approved by the Royal Melbourne Hospital Human Research Ethics Committee (2019.358). The protocol is registered with Australian New Zealand Clinical Trials Registry (ANZCTR 12620001305910).

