### Sample size

To our knowledge, this will be the first study to report feasibility of HMB administration to critically ill trauma patients. Therefore, data will be used to generate sample size estimates for later confirmatory studies [64, 65]. For this trial, a suitable number of participants has been estimated based on admission data at the host institution. A recent observational study was able to recruit 28 patients over a 6-week period using a similar eligibility criteria [4]. Accounting for attrition associated with obtaining written informed consent, it is estimated to be feasible to recruit 50 participants over a 18-month period [65]. If participant recruitment is significantly less than this, the study can be extended for an additional 6–12 months.

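### The primary recruitment rate leaves out patients with an exclusion criterion, yet refused consent, late consent and logistic reasons are exclusions, so the rate sits near 100% and cannot show consent losses

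*Protocol article*

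**What the plan says.** The Primary outcomes section of the protocol article fixes the population for the recruitment rate twice: once in the list of primary outcomes, and again in the list of indicators to be reported, as the percentage "of patients who meet all of the inclusion and none of the exclusion criteria are recruited".

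Table 1 (Study participants) lists eleven exclusions. Six are clinical: inevitable death, bilateral above-knee amputation, complete or predominant parenteral nutrition, pregnancy, primary neuromuscular pathology and presumed cord transection. Four others concern consent or logistics:

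- "Medical decision treatment maker, participant or medical practitioner declined consent"
- "Unable to obtain consent within 7 days from initial traumatic injury"
- "Limited research availability over enrolment timeframe"
- "Enrolment conflict with other research studies"

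The eleventh, a judgement that the patient is unlikely to take part in long-term follow-up, could be placed in either group.

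The Sample size section cites a reference accrual: "A recent observational study was able to recruit 28 patients over a 6-week period using a similar eligibility criteria". It continues: "Accounting for attrition associated with obtaining written informed consent", "it is estimated to be feasible to recruit 50 participants over a 18-month period". It does not quantify that attrition and states no expected recruitment percentage.

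**The concern.** A recruitment rate in a feasibility trial should show what share of suitable patients can be brought into the study. The usual ways of losing a suitable patient are refusal, failure to reach a decision maker in time, absence of research staff, and a competing study. Here each of these is an exclusion criterion, and the denominator admits only patients with no exclusion criterion. The losses that the rate should measure are therefore removed before it is calculated.

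Recruitment is named under Study objectives as a component of feasibility, and the Abstract says the results will inform a larger trial. A percentage near 100% would give the planners of that trial no guide to the consent fraction or to the number of patients they must screen.

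**Working it through.** **The plan's own figure.** There is no stated recruitment percentage to reproduce. The target of 50 cannot be reproduced either, because the consent attrition applied to the reference accrual is not given. The check is therefore of the definition itself.

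**Two definitions.** Let R be the number recruited, L the number lost only through the four consent or logistic exclusions, and M the number who meet every criterion but are not recruited for an unlisted reason (missed at screening, or consented and not randomised).

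- As written: R / (R + M). L does not appear.
- Over clinically eligible patients: R / (R + L + M).

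**Step 1: no unlisted losses (M = 0), R = 50 from the protocol, L assumed.**

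| L (assumed) | As written | Over clinically eligible |
|---|---|---|
| 0 | 50/50 = 100% | 50/50 = 100% |
| 25 | 50/50 = 100% | 50/75 = 67% |
| 50 | 50/50 = 100% | 50/100 = 50% |
| 100 | 50/50 = 100% | 50/150 = 33% |

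The written rate does not move as the losses grow.

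**Step 2: allow some unlisted losses.** Take 100 clinically eligible patients, assume 5 are missed for an unlisted reason, and let a fraction c of the other 95 be recruited, the rest being lost under a listed exclusion. The written rate is 95c / (95c + 5).

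| c (assumed) | As written | Over clinically eligible |
|---|---|---|
| 0.90 | 85.5/90.5 = 94.5% | 85.5% |
| 0.50 | 47.5/52.5 = 90.5% | 47.5% |
| 0.14 | 13.3/18.3 = 73% | 13.3% |

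The written rate can fall below 100%, but only because of the five missed patients. With M = 0 it returns to 100% at every value of c. No refusal is ever counted as a failure to recruit.

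**The case against.** **Eligibility may be meant to come before consent.** The Study participants section describes screening and identification of eligible patients first, and the seeking of consent afterwards. On that reading the consent items are only loosely placed in Table 1, and one clarifying sentence would cure the problem. The reading is plausible and may be the intention. It does not remove the conflict, because the indicator refers to the exclusion criteria without reservation and Table 1 includes the consent items among them.

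**Refusals may be visible elsewhere.** The protocol commits to CONSORT reporting and has a modified CONSORT diagram, whose content is not available here. It may well show exclusions by reason, so it cannot be said that the losses will go unreported. The named primary indicator would still not reflect them.

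**Little turns on the rate.** No threshold or progression rule is attached to it in the Primary outcomes section. Retention is calculated among enrolled patients and is unaffected, as are the blinding and dose-consumption indicators and the randomised comparison. If reasons are logged, the rate can be recalculated later. All of this stands, and it limits the damage to one indicator. That indicator is nonetheless a primary outcome.

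**Two stronger readings are not supported.** A reader might infer that the rate is 100% whatever happens. It is not: patients missed for unlisted reasons, or consented and not randomised, still lower it. A reader might also extrapolate the reference accrual (28/6 × 78 weeks = 364) and conclude that the protocol implies a true recruitment rate of 50/364 = 13.7%. It does not. The 28 were patients already recruited to an observational study with similar, not identical, criteria; steady accrual over 78 weeks is assumed; and 50 is a chosen target, so the ratio reflects the planned sample size and not consent losses.

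**Conclusion.** The point holds. The stated denominator and Table 1, taken together, exclude refusals and most logistic losses from the primary recruitment rate, push it towards 100%, and stop it showing the consent attrition that the Sample size section allows for. This is a rule the protocol states, not a detail left to a later document.

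The size depends on losses that the protocol does not quantify. For assumed losses of 25 to 100 patients against 50 recruited, the written rate overstates recruitment among clinically eligible patients by 33 to 67 percentage points (100% against 67% to 33%). These figures assume that every non-recruited patient falls under a listed exclusion; unlisted losses would bring the written rate down somewhat.

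The conclusion does not extend to saying that consent or logistics is the main constraint on the trial. The Sample size section mentions consent attrition only, and does not rank it.

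**What to change.** For this indicator only, define the denominator as screened patients who meet the inclusion criteria and none of the six clinical exclusions. Count declined consent, no consent within seven days, limited research availability and study conflict inside that denominator, tabulated as reasons for non-recruitment. State whether a patient judged unlikely to take part in long-term follow-up is treated as ineligible or as not recruited, and report that number separately, since either convention can be defended.

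The criteria for enrolment, the procedures and the sample size stay as they are. The cost is a rewording of the indicator, one extra split of the screening log, and a reported rate that will look less favourable. Consented over approached, and participants per month with any extension months shown apart, would be useful additions but are optional.

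### The primary adherence outcome has two denominators, intended and prescribed doses, so the reported figure can exceed the one defined

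*Protocol article*

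**What the plan says.** Under Primary outcomes, the article lists three ways of quantifying feasibility and then three indicators to report. The third outcome is the "amount of HMB supplementation actually consumed compared to the amount intended with full protocol" compliance. The third indicator is the percentage "of the prescribed HMB supplementation doses consumed".

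Trial intervention and control describes the data behind them: "The number of doses prescribed and consumed will be recorded for the duration of the study". It also says: "The intervention or control will be documented in the electronic medication record by the treating team and administered by the nurse caring for the patient". Reasons for missed doses are to be noted, but the article does not say whether an intended dose that was never prescribed counts as missed.

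The intended schedule is stated. "Patients will receive the intervention or control from day 1 post enrolment until hospital discharge or study day 28, whichever occurs first". After a readmission within 28 days of randomisation, "study procedures and administration of the intervention or control will resume". Table 2 places administration in the column "Daily from day 1–day 28 or hospital D/C". On the amount per dose: "Three grams of HMB is dissolved in 150 ml of fluid".

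**The concern.** One primary outcome is given two denominators. The protocol's schedule and the patient's hospital stay fix the intended amount. Prescribed doses are a count recorded during the trial, and that count can fall short of the schedule. An intended dose that is not prescribed is a shortfall in delivery under the outcome, yet it does not enter the indicator at all.

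This matters here because the Background says it is unclear whether a blinded nutrition intervention can be continued after ICU discharge, and the results are meant to inform a larger trial. An adherence figure that combines non-prescription with non-consumption, or omits the first, says less about whether the supplement can be delivered over the whole stay. Two analysts could also follow different sentences of the same section and report different values for a primary outcome.

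**Working it through.** The article states no adherence figure or threshold, so there is nothing to reproduce. The check compares the two ratios.

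Inputs from the article:
- Outcome: consumed over intended (Primary outcomes).
- Indicator: consumed over prescribed (Primary outcomes).
- Longest dosing period: 28 days, with daily administration (Trial intervention and control; Table 2). At one 3 g dose a day, this is 28 doses, or 28 × 3 = 84 g.

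Inputs assumed, because the article does not give them:
- Intended doses never prescribed: 0 to 7 of 28 (0% to 25%).
- Share of prescribed doses consumed: 80%, with a range of 70% to 90%.
- Each dose is taken in full or not at all, so that ratios of amounts and of doses coincide.

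Let C be doses consumed, P doses prescribed and I doses intended. Then

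C/I = (C/P) × (P/I).

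So C/P = (C/I) × (I/P). The two are equal when P = I. When P is smaller than I and C is above zero, C/P is larger by the factor I/P. The absolute gap is (C/P) × (1 − P/I). The indicator could err the other way only if more doses were prescribed than intended.

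With I = 28 and C = 0.8 × P, where C is an expected count:

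| Intended doses not prescribed | P | C | C/P | C/I | Gap (points) |
|---|---|---|---|---|---|
| 0 | 28 | 22.4 | 80.0% | 80.0% | 0.0 |
| 1 | 27 | 21.6 | 80.0% | 77.1% | 2.9 |
| 3 | 25 | 20.0 | 80.0% | 71.4% | 8.6 |
| 5 | 23 | 18.4 | 80.0% | 65.7% | 14.3 |
| 7 | 21 | 16.8 | 80.0% | 60.0% | 20.0 |

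Varying consumption with 7 doses not prescribed:
- C/P = 70%: C/I = 0.7 × 21/28 = 52.5%, a gap of 17.5 points.
- C/P = 90%: C/I = 0.9 × 21/28 = 67.5%, a gap of 22.5 points.

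The gap depends on the share of doses not prescribed, so the same number weighs more in a short stay. With 3 of 14 intended doses not prescribed, C/I = 0.8 × 11/14 = 62.9%, against 71.4% for 3 of 28.

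**The case against.** The best defence is that the indicators follow the outcomes in the same order, so the third indicator may simply be the working form of the third outcome, with *prescribed* meaning prescribed by the protocol. The two would then agree. The text does not define the word, so this reading cannot be excluded. It is the less natural one, because the article records the number of doses prescribed as a count beside the number consumed, which points to doses actually ordered. Even if the defence is right, a primary outcome should not depend on a reader's choice between two meanings.

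A reader might infer more than the text supports:
- *That adherence will be overstated.* The article neither says nor suggests that prescribing will fall short of the schedule. If every intended dose is prescribed, the gap is zero.
- *That lapsed orders would be invisible.* Administration is followed daily, doses prescribed and consumed are counted, and the schedule is fixed. A shortfall could be recovered from the planned data, although the stated indicator would not show it.
- *That the article says the treating team prescribes the doses.* It says the team documents the product in the medication record. That *prescribed* means ordered there is an inference.
- *That restricting the indicator to HMB is an error.* HMB can be consumed only in the HMB arm, and compliance is documented for both arms. Reporting the control arm too is a preference.

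It is also fair to say that no stated progression rule turns on the adherence figure. That limits the stakes but does not reconcile the two sentences.

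**Conclusion.** The point holds in conditional form. The article defines a primary feasibility outcome against intended doses and reports it against prescribed doses. On the natural reading of *prescribed* these can differ. To the extent that intended doses are not prescribed, the reported figure exceeds the defined one by the factor intended/prescribed.

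The direction is arithmetic. The size is not known from the article: it is 0 to 20 points if 0 to 7 of 28 doses are unprescribed and 80% of prescribed doses are consumed, and up to 22.5 points if 90% are consumed. This is an inconsistency to settle before analysis. It is not evidence that the trial's adherence result will be wrong.

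**What to change.** Make consumed ÷ protocol-intended doses the primary adherence indicator, to match the outcome already stated.

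- **Intended doses:** the daily doses due from day 1 to the earliest of hospital discharge, death or day 28, plus in-hospital days after a readmission within the 28 days, as the article's own schedule provides. Nothing in dosing or care changes.
- **Unprescribed doses:** count an intended dose that was not prescribed as missed.
- **Withdrawal:** the Withdrawals section lets participants leave by choice or on the consultant's judgement. State whether days after withdrawal stay in the denominator, for example by showing the result with and without them, because retention is a separate indicator.
- **Components:** report consumed ÷ prescribed and prescribed ÷ intended beside the primary figure. Their product is the primary figure, and they separate non-consumption from non-prescription.

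The cost is one derived variable, built from the daily administration record and the dates of hospital stay, death and any readmission. The only other downside is that the adherence figure may be less favourable.
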